### Trial conditions

#### CA programme

The programme will consist of six face-to-face group-based sessions lasting up to 90 min of a structured exercise programme with integrated educational and lifestyle modules, and a psychological component delivered at the recruiting hospital sites. Exercise sessions have been reviewed by a physiotherapist with experience working with patients with heart conditions and a child cardiologist who have deemed the exercise safe for CYP to engage in. Patients are free to stop the exercise if they begin to feel unwell. Lifestyle modules will focus on modifiable risk factors. The psychological treatment component (MCT) is integrated throughout each session and focuses on controlling worry and using adaptive attention strategies. Sessions include group discussions, experiential learning and homework tasks that participants are asked to complete between sessions. Participants in this treatment arm will also receive routine clinical outpatient management (TAU) alongside CR.

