### Outcomes

The primary outcomes of the study are feasibility and acceptability outcomes. Feasibility will be assessed using referral rates, recruitment (ie, number of patients consented and randomised, number of patients declined the study) and retention rates (ie, number of patients withdrawn from the study, lost to follow-up) and attendance at the intervention. Qualitative semistructured focus groups or interviews, as preferred, will be used to understand CYP, caregivers and healthcare professionals’ views of acceptability of the intervention and targets for improvement. All outcomes listed below will be obtained at each assessment time point.

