#### Incremental Shuttle Walk Test

The Incremental Shuttle Walk Test (ISWT)^53^ is used to assess exercise capacity. The ISWT is a 12-level test (1 min in each level), whereby participants walk up and down a 10 m course with increasing acceleration of 0.17 m/s up to a maximum speed of 2.37 m/s. The walking speed is dictated by an audio signal. The test ends when the subject has a heart rate greater than 85% of their predicted maximum, is limited by dyspnoea, or when the subject is unable to maintain the required speed and does not complete a shuttle for a second consecutive time. The distance covered from the number of shuttles will be calculated.

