### Safety reporting

Adverse events (AEs) and serious AEs (SAEs) will be monitored throughout the study. AEs are defined as any untoward medical occurrence in a patient or study-specific intervention and which does not necessarily have a causal relationship with the intervention (ie, deterioration in cardiac health not associated with the intervention). SAEs are defined as AEs that result in death, are life-threatening or require hospitalisation. Adverse reactions (ARs) are an untoward medical or unintendical medical response in a patient to a study specific intervention which has a causal relationship with the intervention (ie, physical injury due to the intervention). Serious ARs (SARs) are defined as ARs that result in death, are life-threatening or require hospitalisation. All AEs, SAEs, ARs and SARs will be reviewed by the trial’s child clinical psychologist and paediatric consultant cardiologist within 24 hours of reporting. Any AEs identified as likely to be caused by the intervention during the period of recruitment or intervention on the study will be recorded at the study site using an AE/SAE record form which will be completed by the health professionals. Study RA and study PIs will be informed, and information inputted onto a secure database. The CIs will also assess if the nature of the event is likely to have been induced because of the study intervention or processes. Any that are deemed be serious and related to the intervention will be reported to the sponsor, the study executive committee and ethics committee within 24 hours of the event.

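### Causality is judged against the intervention or study processes, but the rule for reporting serious events to the sponsor and ethics committee covers only those related to the intervention

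*Protocol article*

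**What the plan says.** All statements below are in the Protocol article.

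**Safety reporting** sets out four steps.
- Clinical review covers everything: "All AEs, SAEs, ARs and SARs will be reviewed by" the trial's child clinical psychologist and consultant paediatric cardiologist, within 24 hours of reporting.
- Recording on the AE/SAE form is limited by cause: "Any AEs identified as likely to be caused by the intervention during the period of recruitment or intervention on the study will be recorded".
- Causality assessment is wider: "The CIs will also assess if the nature of the event is likely to have been induced because of the study intervention or processes".
- Escalation returns to the narrower scope: "Any that are deemed be serious and related to the intervention will be reported to the sponsor, the study executive committee and ethics committee".

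The definitions of adverse reaction and serious adverse reaction in the same section refer to a causal link with the study intervention only.

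**Study procedures that involve exertion.** The 6-minute walk test (6MWT) and the Incremental Shuttle Walk Test (ISWT) are among the measures, and the Outcomes section states: "All outcomes listed below will be obtained at each assessment time point". No restriction by arm is given. The ISWT is externally paced with rising speed. One of its end criteria is a heart-rate limit: "The test ends when the subject has a heart rate greater than 85% of their predicted maximum". Breathlessness and failure to keep pace are the others.

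**Oversight.** Trial management and oversight arrangement places the chief investigator, coinvestigators and principal investigators on the executive committee, which has operational responsibility for conduct and for safeguarding patients.

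**The concern.** Two consecutive sentences in one paragraph use different causal scopes. The investigators are asked whether the intervention or a study process caused the event, but only one of those two answers has a stated consequence. If the answer is a study process, the article requires no report to the sponsor or to the ethics committee, however serious the event.

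This matters because the trial's assessments include two exercise tests in children who may have cardiomyopathy, arrhythmia or heart failure. Usual-care children receive no trial intervention but do the same tests. Under the current definitions, related serious events can therefore exist in one arm only, although both arms undergo the same study-imposed exertion. The trial is meant to inform a definitive trial, and harms attributable to its outcome tests are part of that information.

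**Working it through.** The article gives no figure to reproduce here. The check is a comparison of text, followed by a count of exposure.

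**Step 1. Causal scope of each element in Safety reporting**

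| Element | Scope as written |
|---|---|
| Clinical review within 24 hours of reporting | All events, any cause |
| Adverse reaction and serious adverse reaction definitions | Intervention |
| Entry on the AE/SAE form | Likely caused by the intervention |
| Causality assessment by the chief investigators | Intervention or study processes |
| Report to sponsor, executive committee, ethics committee | Serious and related to the intervention |

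Study processes appear only in the assessment row. No other row attaches a reporting duty to them.

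**Step 2. Where a serious event caused by a walk test goes.** It is reviewed by the two clinicians. It is assessed by the chief investigators, who may attribute it to a study process. It does not meet the serious adverse reaction definition, the form-entry condition or the escalation condition.

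**Step 3. How many planned tests this concerns.** Inputs:
- 100 children, 50 per arm (Sample size calculation);
- 2 walk tests (Measures);
- 3 time points: baseline, 12 and 24 weeks (Data collection);
- all measures at each time point (Outcomes);
- baseline data collected before randomisation (Recruitment and allocation).

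Counts:
- Total: 100 × 2 × 3 = 600.
- Baseline, before randomisation: 100 × 2 × 1 = 200.
- Follow-up, usual care: 50 × 2 × 2 = 200.
- Follow-up, CardioActive: 50 × 2 × 2 = 200.
- In children with no exposure to CardioActive: 200 + 200 = 400, and 400 / 600 = 67%.

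**Step 4. Sensitivity to drop-out.** Assume that 20% of each arm, the rate used in the sample size section, are missing at both follow-ups.
- Each follow-up group falls to 0.8 × 200 = 160.
- Total: 200 + 160 + 160 = 520.
- No exposure to CardioActive: 200 + 160 = 360, and 360 / 520 = 69%.

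For these 400 (or 360) tests, relatedness to the intervention is impossible by construction. For the 200 follow-up tests in the CardioActive arm it is possible, but an event caused by the test alone would still fall outside the rule.

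**The case against.** **The executive committee would know.** A reader might infer that such an event never reaches the sponsor, the executive committee or the ethics committee. The documents do not support that. The chief investigator, who takes part in the causality judgement, sits on the executive committee with the coinvestigators and principal investigators, so members of that committee would probably be aware of it. For the sponsor and ethics committee, the supportable statement is that this rule does not require a report, not that none would be made.

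**Other safeguards apply to everyone.** All events in both arms get clinical review within 24 hours of reporting. Children with significant exercise risk are excluded, and clinical teams screen for eligibility. The heart-rate criterion is a limit on the test as well as a sign of its intensity. These points stand. They bear on how likely an event is and on its clinical handling, but do not create a duty to inform the sponsor or ethics committee.

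**The wording may be shorthand, or the full protocol wider.** The article condenses protocol Version 6, which is not shown, and commits to Good Clinical Practice. Both readings are possible. However, the assessment sentence itself separates intervention from processes, and the adverse reaction definitions name only the intervention, so a site could reasonably take the trigger as excluding tests. If Version 6 is wider, the article misstates it.

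**Unreviewed tests.** A reader might also infer that the walk tests had no safety review, because the CA programme section says only: "Exercise sessions have been reviewed by a physiotherapist with experience working with patients with heart conditions and a child cardiologist". Silence in an article about the tests does not show that they went unreviewed.

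**Counts are not risk.** One could set the 600 tests against at most 50 × 6 = 300 session attendances and say that two thirds of study-imposed exercise is uncovered. That equates a short walk test with a session of up to 90 minutes and uses no event rate. Likewise, calling 50 × 2 × 3 = 300 tests usual-care tests includes 100 done before randomisation. The count in Step 3 avoids both problems but still measures exposure only.

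**Evidence on the tests is not wholly lost.** The nested qualitative study covers experience of outcome measures, and the analysis covers missing data and reasons for drop-out. That is correct, but neither replaces reporting of serious harm.

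**Conclusion.** The point holds as an internal inconsistency with a safety consequence. Assessment covers the intervention or study processes. The related-event definitions, form entry and escalation cover the intervention only. A serious event attributed to the 6MWT or ISWT therefore has no written route that requires a report to the sponsor or ethics committee. The article states this rule explicitly, so the point is not about detail left to another document.

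In size, 400 of 600 planned walk tests (67%; 69% under the assumed 20% loss) take place in children for whom an event could not be related to the intervention. The article gives no event rate, so the number of events affected cannot be estimated and may be small.

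Assumptions: the abbreviation CIs in Safety reporting means the chief investigators; the study executive committee named there is the trial executive committee described under oversight; both walk tests are done by all children at all three time points, as the Outcomes section states (the schedule figure is not shown); and the full protocol does not already carry a wider rule.

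**What to change.** Reconcile Safety reporting so that one causal scope, related to the intervention or to any study procedure, is used throughout and in both arms:

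1. In the definitions of adverse reaction and serious adverse reaction.
2. In the sentence on which events are entered on the AE/SAE form.
3. In the escalation sentence, so that serious events related to the intervention or to any study procedure go to the sponsor, executive committee and ethics committee.
4. On the AE/SAE form, add a field for the attributed source (CardioActive session, homework, walk test, other), completed for both arms.

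If Version 6 already uses the wider scope, only the published wording needs correcting. Otherwise the change is a few sentences and one form field, submitted as an amendment. The downside is that slightly more events will be recorded and escalated. Sample size, outcomes and the planned analyses are unaffected.

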### Ethics and dissemination

The study received full ethical approval on 14 February 2023, from North West—Greater Manchester East Research Ethics Committee, Research Ethics Committee (REC) REC ref: 22/NW/0367, IRAS ID 319134. The trial has been registered with ClinicaTials.gov (NCT05968521) and with ISRCTN (ISRCTN50031147). The study protocol used was Version 6: 21 June 2023. Any modifications to the trial will be submitted for further ethical approval and approved changes will be documented and communicated to the REC, trial registry, executive committee and all relevant parties. The study will be conducted in accordance with the ethical principles that have their origin in the Declaration of Helsinki (1996), the principles of Good Clinical Practice and the UK Policy Framework for Health and Social Care Research (2017). GMMH acts as the sponsor for this study. As the sponsor is an NHS organisation, the NHS indemnity scheme will apply. Participating sites will be liable for clinical negligence and other negligent harm to participants taking part in the study and covered by the duty of care owed to them by the sites concerned.

Written informed consent will be obtained from all participants and their parents/caregivers. Participants will be free to withdraw from the study at any time without providing a reason or their care being impacted. All the information collected during this trial will be confidential and held in accordance with NHS Data Protection guidelines and Good Clinical Practice guidelines. Confidentiality will only be breached if participants disclose information, which may indicate that there is a risk of harm to themselves or others. Every opportunity to discuss any possible breaches of confidentiality with participants will be taken prior to informing any appropriate agencies, for example, children and adolescent mental health services, general practitioner (GP) or accident and emergency (A&E) services.

All researchers and study site staff involved with the study must comply with the requirements of the Data Protection Act 1998 regarding the collection, storage, processing and disclosure of personal information, and will uphold the Act’s core principles. Audiorecordings and transcriptions of interviews will be stored on NHS drives, which are password protected and designed for the storage of confidential research material. Interviews which are transcribed will be anonymised at the point of transcription. Any third party involved with transcribing of interviews will sign a confidentiality agreement and be fully instructed in how to anonymise transcripts.

The main study results will be published in the name of the study in a peer-reviewed journal, on behalf of all collaborators. The manuscript will be prepared by a writing group, appointed from among the TEC. All participating centres and clinicians will be acknowledged in this publication. All presentations and publications relating to the study must be authorised by the study executive committee and sponsor, on whose behalf publications should usually be made. Authorship of any secondary publications resulting from the intervention will reflect the intellectual and time input into these studies and will not be the same as on the primary publication. No investigator may present or attempt to publish data relating to this study without prior permission from the TEC . The findings will also be presented at national, international and regional conferences and in public involvement events where the information from this study is relevant.

### Patient and public involvement

A youth PPI group composed of young people with lived experience of a heart condition (with and without mental health difficulties) has been created along with an adult PPI group comprised of parents, caregivers and adult heart condition patients (with and without mental health difficulties). Both PPI groups have aided in the development of the CA programme, in obtaining ethical approval, codeveloped patient-facing materials, helped to develop the patient recruitment and retention plan, have helped to develop the study name and logo, and will further assist with retention, development of the dissemination plan and with dissemination of research findings.

## Discussion

CHD presents as one of the most common non-communicable childhood diseases. While medical advances have improved survival rates, young people with heart conditions continue to face significant challenges, comorbidities, reduced quality of life and increased psychological distress. NHS England has highlighted that cardiac services must be provided in a way that allows the best outcomes for all patients, not only in reducing mortality, but also in decreasing disability and improving opportunities to lead better lives.^66^

A CR programme that integrates mental and physical healthcare has the potential to meet NHS objectives^67^ which aims to ensure that CYP, their family and carers have an understanding of the patient’s condition, its impact on their health and future, and an understanding of the condition’s psychological, social and cultural factors in addition to service specifications for cardiac disease.^68^

The current study is limited by the sample size, and it is not powered to evaluate efficacy of the intervention. Despite this, the study will attempt to provide data on important logistical and clinical outcomes, which will help inform the power calculation for a full trial.

Despite the limitations, this study would meet service standards and fits within current priorities for closer integration of psychological and physical health services.^19 20 69^ Development and evaluation of a CR programme is an important platform for the progression of young person’s cardiac services and will provide valuable qualitative and quantitative data to support the design of a future large-scale definitive trial to test the effectiveness of CA for CYP with CHD.
